## Abstract

**Background:**

Performance anxiety represents a significant challenge for students, manifesting as a fear of failure and difficulties managing examination-related concerns and academic pressures. According to recent statistics, anxiety affects >4% of the global population, underscoring the need for effective management methods. Studies indicate that yoga and virtual reality (VR) training can alleviate symptoms of performance anxiety.

**Objective:**

This trial aims to compare VR-assisted cognitive behavioral therapy (CBT) with yoga interventions to find effective treatments.

**Methods:**

A single-blinded randomized controlled trial will be conducted with 60 participants (n=30, 50% per intervention group) recruited from university and preuniversity counseling centers. The trial will measure whether the interventions reduce performance anxiety in students. Stratified randomization will be used to ensure equal distribution of baseline anxiety levels and gender across both groups. The primary outcome is a reduction in anxiety, measured using the State-Trait Anxiety Inventory-Y1 and State-Trait Anxiety Inventory-Y2 subscales. Secondary outcomes include emotional regulation and quality of life. Data will be collected at baseline, after the intervention, and during follow-up assessments. Statistical analyses will include parametric tests (eg, repeated-measures ANOVA and *t* tests) to compare anxiety reduction, emotional regulation, and quality of life across groups. The intention-to-treat approach will be applied to minimize bias due to participant dropouts. Sensitivity analyses will assess the robustness of the findings.

**Results:**

This study is planned to start in September 2025 and end in June 2026. VR-assisted CBT is expected to reduce anxiety very quickly, whereas yoga is predicted to have long-term benefits.

**Conclusions:**

More generally, this research highlights the need for new, accessible forms of mental health support. VR-assisted CBT is an emerging digital mental health intervention, and it enables individuals to access and explore anxiety in virtual, safe environments. In contrast, yoga is a more conventional, all-encompassing discipline that enhances mental health through physiological and psychological processes that may have long-term effects.

**Trial Registration:**

ClinicalTrials.gov NCT06639841; https://clinicaltrials.gov/study/NCT06639841

**International Registered Report Identifier (IRRID):**

PRR1-10.2196/66112

## Introduction

### Background

Performance anxiety represents a significant challenge for many students, manifesting as an intense fear of failure and difficulties managing concerns associated with examinations and other academic activities. Recent international statistics [1,2] identify anxiety as one of the most prevalent issues globally, affecting >4% of the world population. In this context, alternative anxiety-reducing methods, such as yoga and virtual reality (VR) training, have gained increased attention both academically and practically. Recent research suggests that yoga practices and training using VR techniques can play a crucial role in alleviating performance anxiety symptoms.

As a mind-body practice, yoga offers a holistic approach that can help reduce anxiety symptoms by regulating the autonomic nervous system and reducing stress responses. By integrating poses (asanas), breathing techniques (pranayama), meditation, and deep relaxation, yoga can modulate brain activity and cortisol levels, thereby improving mental health. Regarding yoga-specific techniques, several experimental studies indicate a significant reduction in anxiety and an overall improvement in well-being through practices of meditation and breathing exercises [3-6]. These studies suggest that these techniques reduce anxiety through physiological and psychological mechanisms, including cortisol reduction and enhanced emotional regulation, and are effective in various contexts (eg, high-performing music students as well as students with lower academic performance). These findings are partially supported by a meta-analysis that highlights the positive effects of yoga on psychophysiological parameters associated with performance anxiety, such as heart rate and its variability, while also noting that further studies are needed to confirm their usefulness in reducing clinically diagnosed anxiety [7].

Specific research on evaluation anxiety in the literature mainly includes general studies, with only a few examining anxieties in various performance situations. Zoogman et al [8] reported significant outcomes from yoga interventions, drawing from controlled clinical research with diverse contexts, indicating the global effectiveness of yoga programs on anxiety symptoms. Another literature review underscores the efficacy of yoga programs for children and adolescents aged <18 years [9]. Although these studies have several methodological limitations, their findings indicate a general reduction in anxiety. In addition, Khalsa et al [4] showed that a 6-week program for music students significantly reduced music performance anxiety, with notable outcomes both at the end of the program and compared to a control group. Erdoğan Yüce and Muz [10] tested an intervention program for young people aged 18 to 25 years, where a yoga program including asanas (physical poses), pranayama (breathing exercises), and meditation contributed to improved physical and mental health. Conducted over 4 weeks with 60-minute sessions, the quasi-experimental study found a significant reduction in state anxiety but not trait anxiety. The program’s social quality of life (QoL) improved due to group interactions during the sessions, although the number of yoga sessions was limited and insufficient for significant trait-level changes.

Although the broader literature indicates some limitations in yoga research, Li and Goldsmith [11] identified specific issues, such as small sample sizes, control groups, and random group allocation. In addition, they highlighted the importance of intervention duration in anxiety and stress outcomes. For example, Rocha et al [12] found the best yoga intervention outcomes after 6 months, significantly reducing anxiety and other psychological health aspects. Participants were yoga naive, and the results were measured alongside a control group at the beginning of the intervention and after 6 months. Shohani et al [13] noted significant results after a substantial number of sessions (eg, 12 sessions) on various mental health aspects, including anxiety. In another study, the authors proposed a program for testing in 2021 [14] and synthesized the literature by collecting data from experienced yoga practitioners. They concluded that at least 10 yoga sessions significantly reduced anxiety symptoms and improved sleep, with participants reporting decreased anxiety severity and improved sleep quality after 10 sessions without significant adverse effects. The findings suggest that yoga can serve as an effective complementary treatment for anxiety; however, more extensive clinical studies are required to confirm its efficacy. Finally, Nanthakumar [15] synthesized the literature and analyzed randomized clinical research, finding that yoga positively impacted anxiety and depression symptoms across 8 studies involving interventions from 4 to 6 months.

Research indicates effectiveness regarding the impact of VR-assisted psychoemotional support, particularly when specific cognitive behavioral techniques are implemented [16]. In a recent dissertation [17], safe exposure to a virtual concert auditorium helped student artists reduce state anxiety. Similarly, Bissonnette et al [18] tested these techniques on music students with performance anxiety, demonstrating that one hour-long sessions across 3 weeks significantly reduced performance anxiety. Following short-term cognitive behavioral therapy (CBT) principles, this approach’s effectiveness highlights the potential for fewer sessions (eg, 4 sessions in a controlled experimental protocol) [19]. Finally, recent meta-analyses [20] indicate the superior efficacy of VR therapies compared to control groups, although they do not exceed the effectiveness of in vivo exposure.

Existing literature not only suggests that both intervention programs are effective but also reveals numerous research limitations. Hoge et al [21] compared yoga with cognitive behavioral and educational programs but not VR-assisted techniques, showing that yoga and CBT are more significant than educational methods. Although yoga shows promising results among students, compared to VR-assisted techniques, it is studied in general context and very few studies are specifically comparing them. For instance, Chauhan et al [22] demonstrated the effectiveness of a yoga program for medical students using these techniques to address anxiety and mental health aspects. Moreover, there is limited research testing intervention program efficacy for both state and trait anxiety. For instance, Somere et al [23] found that online yin yoga sessions for 2 hours per week significantly reduced state anxiety after each session, although the results of trait anxiety were less conclusive. O’Shea et al [24] noted that CBT is the standard psychological treatment for anxiety disorders. However, some individuals either do not access the treatment or do not benefit significantly from CBT alone. Finally, yoga, as a holistic mind-body practice, is seen as a potential CBT complement, providing benefits such as reduction in stress, anxiety, and depression through mindfulness, breathing, and movement techniques.

Previous research on VR-assisted CBT (VR-CBT) has predominantly focused on its efficacy in treating social anxiety, phobias, and generalized anxiety, often comparing it to passive relaxation or mindfulness-based interventions. However, these comparisons have largely assessed meditation, guided breathing, and progressive muscle relaxation without incorporating structured movement-based interventions such as yoga. This study addresses a critical gap by directly comparing the effects of VR-CBT with yoga, which extends beyond passive relaxation through the integration of physical postures (asanas), controlled breathing techniques (pranayama), and ethical self-discipline (Yama and Niyama). Unlike meditation alone, yoga actively engages both the body and mind, promoting physiological regulation of stress through autonomic nervous system modulation and improving emotional regulation via structured movement and breathwork. Previous studies have shown that VR-CBT provides rapid symptom relief through immersive exposure and cognitive restructuring, while meditation and relaxation techniques tend to cultivate mindfulness without the added physical benefits of yoga. By assessing yoga as a distinct intervention, this study aims to determine whether its multimodal approach leads to more sustainable long-term reductions in performance anxiety compared to the short-term but potentially more immediate effects of VR-CBT. The findings will offer new insights into the comparative efficacy of digital and traditional mind-body interventions for academic anxiety, contributing to the development of more tailored therapeutic strategies.

### Goal of This Research

This research aims to evaluate and compare the effectiveness of 2 psychological intervention modalities—VR-facilitated exposure techniques based on cognitive behavioral intervention and yoga techniques involving body posture, breathing, and meditation—in reducing performance anxiety symptoms. In addition, the study seeks to investigate whether VR techniques lead to a more significant reduction in state anxiety, while yoga techniques are more effective in reducing trait anxiety.

## Methods

### Research Design

#### Overview

This study is structured as a parallel group randomized controlled trial (RCT) comparing 2 distinct interventions. It uses a stratified randomization approach to account for variations in baseline anxiety levels and gender.

#### Blinding

Outcome assessors and data analysts will be blinded to group assignments to minimize potential biases.

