The participants will then start the psychoemotional support program and complete an anxiety level assessment at the end of each intervention session. At the end of the program, participants will complete the anxiety questionnaire again, along with an instrument assessing their comfort, discomfort, and the quality of the specific intervention techniques. To evaluate manifestations of performance anxiety, correlations between clinical anxiety and academic anxiety will be checked to indicate the strength and significance of their relationship. Details about the implementation of the techniques are presented in Table 1.

**Table 1 table1:** Overview of intervention components for virtual reality (VR)–assisted cognitive behavioral therapy (VR-CBT) and yoga-based interventions.

Intervention and phase		Session components	Duration

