### VR Cognitive Behavioral Intervention and Theoretical Background

The psychoemotional support intervention, facilitated by VR exposure techniques (6-10 sessions), uses Guided Meditation VR software and stand-alone Oculus Quest 2 and HTC Vive Flow hardware for alleviating performance anxiety. These consist of approximately 6 to 10 sessions of 20 to 30 minutes each of psychoemotional support based on cognitive behavioral techniques and integrative psychotherapy (with extension to a maximum of 1 h, if necessary). They will be carried out over a period of 2 weeks, up to a maximum of 1 month if it is not possible to organize the sessions in optimal conditions. After 1 month, the participants are reported as having withdrawn (in case of a request from the participants) or dropped out of the psychoemotional support program. The initial sessions (1-2 sessions) are designed for psychological assessment, psychoeducation, and familiarization with VR exposure techniques. In the next 2 to 3 sessions, different VR scenarios are tested to find a comfortable virtual environment for each patient. We test if patients agree that they are present in that generated virtual environment in a manner comparable to exposure in a natural environment (eg, a walk by the beach, in a forest, or an underwater itinerary). At this stage, subsequent exposure techniques will be developed using a combination of cognitive restructuring and relaxation methods, aimed at familiarizing participants with the technology and ensuring a pleasant experience. The next 1 to 2 sessions will continue with exercises already chosen, based on cognitive restructuring techniques combined with relaxation techniques. The last session is designed to review one of the exercises, assessing the quality of the technique and offering suggestions for improvement by going through a set of questions (eg, QoL through the QoL questionnaire). Each session concludes with a brief clinical assessment of anxiety using the State-Trait Anxiety Inventory (STAI) tool. Specific manifestations of performance anxiety are assessed.

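### The blinding statement promises blinded outcome assessors, but the listed efficacy outcomes are completed by participants who know their arm, so assessor blinding does not protect them

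*Protocol article*

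**What the plan says.** The Abstract (Methods) states: "A single-blinded randomized controlled trial will be conducted with 60 participants". Under Research Design, the Blinding section is one sentence: "Outcome assessors and data analysts will be blinded to group assignments", given there as a means of reducing bias. It does not define who the outcome assessors are, and it says nothing about participants or facilitators.

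On outcomes, the Abstract says: "The primary outcome is a reduction in anxiety, measured using the State-Trait Anxiety Inventory-Y1 and State-Trait Anxiety Inventory-Y2 subscales", and then: "Secondary outcomes include emotional regulation and quality of life". The Procedure overview says who fills in the anxiety measure: "At the end of the program, participants will complete the anxiety questionnaire again". Participants are also to "complete an anxiety level assessment at the end of each intervention session". The section on the VR intervention adds: "Each session concludes with a brief clinical assessment of anxiety using the State-Trait Anxiety Inventory (STAI) tool". Under Instruments, the emotion regulation measure is described as self-report and quality of life as a questionnaire. Performance anxiety is measured with the Academic Anxiety Inventory, for which no rater is described.

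**The concern.** A reader who sees a single-blinded trial with blinded outcome assessors will normally conclude that knowledge of the arm cannot colour the scores. That conclusion is safe when an independent rater produces the score. Where the participant produces it, the participant is in effect the assessor, and here the participant knows the arm.

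This matters more than usual because the two treatments differ in novelty and in what participants may expect of them, and the protocol itself predicts different profiles. The goal section and the expected results anticipate an advantage for VR on state or early anxiety, and for yoga on trait or lasting anxiety. Unblinded self-report is poorly placed to separate such contrasts from expectancy. If the blinding statement stands, a between-arm difference in STAI may be read as better protected than it is.

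**Working it through.** This is mainly a comparison of text. The arithmetic at the end is only an illustration.

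**Step 1. Who produces each listed efficacy score?**

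| Measure | Status | Who completes it, according to the article |
|---|---|---|
| STAI-Y1/Y2 | Primary (Abstract, Methods) | Participants (Procedure, Overview) |
| Emotion Regulation Questionnaire | Secondary | Described as self-report (Instruments) |
| Quality of Life Inventory | Secondary | Described as a questionnaire (Instruments) |
| Academic Anxiety Inventory | Performance anxiety measure, not named among the Abstract's outcomes | An inventory; no rater described (Instruments) |
| Neurobiological or physiological measures | Mentioned under Sample Size Determination and Results; not listed as outcomes | No instrument given |

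No row gives an independently rated efficacy outcome.

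**Step 2. Do participants know their arm?** They attend either VR headset sessions or yoga sessions, and the Exclusion Criteria refer to two versions of the consent form. Nothing in the article says that participants are masked, and for these two treatments they could not be.

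**Step 3. What does the stated blinding then cover?** The sentence names two groups.
- *Data analysts:* feasible, and nothing contradicts it.
- *Outcome assessors:* for participant-completed forms this can only mean staff who administer or score them. Masking those staff can limit coaching and scoring errors. It does not mask the person whose answers form the score.

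**Step 4. Which STAI score is at issue?** An anxiety assessment closes each session in both arms, and the VR section names the STAI for this. The Abstract separately plans data collection at baseline, after the intervention and at follow-up. The Procedure overview has the questionnaire completed again when the program ends, and Table 1 gives the yoga arm a separate assessment after the intervention. The article does not make a session-end score the primary one, nor does it rule that out.

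**Step 5. Illustration of size.** The article gives 30 per group, 80% power and a 5% level, but no effect size or SD. Its sample size therefore cannot be reproduced, and this point does not depend on it. Take 30 per arm, a two-sided 5% test and no true difference, and assume a between-arm reporting bias of b SD.

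- Standard error of the standardised difference: √(2/30) = 0.258
- Rejection rate: Φ(b/0.258 − 1.96) + Φ(−b/0.258 − 1.96)

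| Assumed b (SD) | b/0.258 | Rejection rate |
|---|---|---|
| 0 | 0 | 5.0% |
| 0.1 | 0.39 | 6.7% |
| 0.2 | 0.77 | 12.1% |
| 0.3 | 1.16 | 21.3% |

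With the t distribution in place of the normal, the figures at 0.2 and 0.3 SD are 11.9% and 20.8%. The values of b are assumptions; the article offers none.

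**The case against.** **Nothing false is said about participants.** Neither the Abstract nor the Blinding section claims that participants are blinded, and the article openly describes two distinct interventions. This stands. Participant blinding is infeasible here and open delivery is no fault. What remains is that the article offers assessor blinding as a safeguard against bias, while its own outcome list leaves that safeguard little to act on.

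**Some protection is real.** A reader might infer that the blinding claim is wholly empty. The documents do not support that: analysts can be blinded, and so can staff who administer or score forms.

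**Session-end STAI is not shown to be the endpoint.** A reader might infer that the primary score is taken in the treatment room at the close of a session. The article does not say so, and it describes baseline, post-intervention and follow-up assessments separately. Nor does it say that a therapist or instructor is present when the endpoint form is completed. The self-report point holds at every time point and does not need this inference.

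**Other measures are mentioned.** It would go too far to say that everything the trial might measure is self-reported, because neurobiological and physiological measures are referred to. They are not defined as outcomes, however, so they do not supply a blinded endpoint. The Academic Anxiety Inventory is also not explicitly labelled self-report.

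**The bias figures are generic.** This stands. They would apply to any unblinded comparison with 30 per arm. Both arms are active, and the authors' predictions favour VR on some measures and yoga on others, so a net bias in one direction is not established. Rewording the blinding statement would not change these rates.

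**Condensed article.** Where and with whom forms are completed may be left to the full protocol. The blinding statement is different: it is an affirmative claim, and further detail elsewhere would not make it accurate for participant-completed outcomes.

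**Conclusion.** The point holds in a limited form. The article presents a single-blinded trial with blinded outcome assessors, but the listed primary and secondary outcomes are a participant-completed inventory, a self-report scale and a questionnaire, in participants who know their arm. No independently rated efficacy outcome is defined. Blinding assessors therefore does not protect measurement of those outcomes, and the statement should be corrected. Analyst blinding, and masking of staff who only handle or score forms, is unaffected.

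The conclusion rests on reading the quality of life questionnaire as completed by the participant, which is its natural meaning, and on the article's own statement that participants complete the anxiety questionnaire. It does not rest on the rejection rates of about 12% and 21%, which show only what an assumed bias of 0.2 or 0.3 SD would do. No actual bias, in either direction, can be inferred from the document. The trial can run as designed; what changes is how it is described, how the endpoint forms are collected, and how firmly a between-arm difference may be interpreted.

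**What to change.** 1. In the Abstract (Methods) and the Blinding section, state that participants and facilitators are unblinded and that the listed efficacy outcomes are participant-reported.
2. Limit the blinding claim to data analysts and to any masked staff who administer or score forms, and say who those staff are.
3. Have the baseline, post-intervention and follow-up STAI used for the primary comparison completed apart from treatment sessions, without the therapist or instructor present. State that session-end scores are not used for that comparison.
4. Commit to interpreting between-arm differences with the limits of unblinded self-report in mind.
5. Optionally, add a one-item expectancy rating in both arms before session 1 and report it beside the result. Its absence is not an error.

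The cost is wording, a minor change in how forms are collected, and a less favourable blinding statement. Sample size and treatment are unchanged.
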